### Who will take informed consent? {26a}

Written documentation of informed consent is obtained before initiating the intervention following approval by the Ethics Committee. The templates for these forms have been developed in collaboration with parent groups and the European Foundation for the Care of Newborn Infants (EFCNI) (see Additional file 2). Each clinical site will adapt the templates for submission to the regulatory authorities in their respective countries. Upon meeting the inclusion criteria, parents or patient’s legal representative will receive a detailed parent information letter, providing extensive information about the trial and intervention. They have the freedom to withdraw their child from the trial at any stage and for any reason, without impacting their child’s ongoing treatment. The investigator or research nurse will obtain separate consent for data collection concerning both the mother and the newborn. Also, a separate consent form for healthcare professionals is developed. Consent forms will be included as part of the process.

### Additional consent provisions for collection and use of participant data and biological specimens {26b}

This trial does not involve collecting biological specimens for storage.

### Interventions

#### Explanation for the choice of comparators {6b}

A cohort of patients, born at clinical sites 1 to 5 from the beginning of the study to the time assigned to start the intervention, will be assigned to the control group, representing standard neonatal care.

#### Intervention description {11a}

The study will start at the same time at all participating sites that will continue to provide routine clinical care according to their current policies. Prospective data gathering will be accomplished.

A start point for the experimental intervention (3, 6, 9, or 12 months from the start of the study) will be assigned for each clinical site (1 to 5) taking into account the expected time internally needed to overcome all logistics and regulatory issues with a potential impact on FICare implementation. A 3-month wash-out period will be used for the local training process and assessment of site readiness, while enrolment will be halted. After that, recruiting will continue, and the experimental intervention will be started. Clinical sites 6 and 7 will run the experimental intervention from the start of the study, without pauses.

##### Training and certification

The RISEinFAMILY training programme is divided into two curricula: for healthcare professionals/staff (Training the trainers) and for families (Education of caregivers), the latter being categorised into two intervention levels (basic and advanced). The following modules are identified as the minimum training contents to be delivered to foster RISEinFAMILY:*Training the trainers:* (1) understanding the boundaries of the FICare model; how to promote FICare among families; (2) psychosocial needs of families (resilience, stress and anxiety, or mourning); communication skills (assertive communication); (3) how to involve families in NICU (safe conduct in NICU environment, attachment and bonding, how to do family-centred medical rounds); (4) professional self-care (burnout, compassion fatigue).*Education of caregivers:* (1) comprehensive description of the FICare model (the strengths and training methodology) and the functional and architectural structure of the NICU; (2) family self-care (stress and anxiety, resilience, or mourning); (3) learning about infants’ neurobehavior, stress and pain; (4) taking part in baby care (basic level), where parents will be “professionalised” as to become the first line care provider of their children; (5) taking part in baby care (advanced level), specific task’s training for infants who require even more specialist care; (6) parents will be prepared for home; a map of the social resources available at the local setting will be provided.

A teacher education system will be used for staff training. Mentor-assigned trainee groups and the calendar for meetings will be defined by site co-ordinators. The procedure will include face-to-face meetings, e-learning tools or a combination of methods adapted to centre facilities and organisational features, in order to accomplish the programme and procedures dissemination among 90% of the NICU staff.

The family training process relays on three cornerstones: (a) individualised theoretical and practical learning by tasks through face-to-face sessions at the cot-side, following an individualised teaching plan adjusted to the baby’s clinical condition and the wish of the parents; (b) family workshops, held as presential, online or hybrid format, that intend to gather parents during 45-min open sessions on relevant topics about the learning contents, to express their doubts and concerns, as well as to share their experiences with other families; (c) registry of teaching activities and task certification once proficiency is fully accredited in a given task, and the family caregiver is allowed to do this task autonomously.

#### Criteria for discontinuing or modifying allocated interventions {11b}

The criteria for discontinuing or modifying allocated interventions for a given trial participant include parents’ request for temporary suspension due to personal reasons or the patient’s worsening condition leading to their desire to withdraw from active participation.

#### Strategies to improve adherence to interventions {11c}

Implementing family-centred rounds and educational workshops allows for continuous evaluation of families’ learning process, fostering better adherence to intervention protocols.

#### Relevant concomitant care permitted or prohibited during the trial {11d}

Implementing the RISEinFAMILY model will focus on the active participation of family members in providing specialised care to their sick newborn baby admitted to the neonatal intensive care unit; this fact will not alter the usual care treatment pathways (including the use of any medication) that will continue for both trial arms.

#### Provisions for post-trial care {30}

 Implementing the RISEinFAMILY model will focus on the active participation of family members in providing specialised care to their sick newborn baby admitted to the neonatal intensive care unit, it will not alter the usual care treatment pathways (including use of any medication) and these will continue for both trial arms.

### Outcomes {12}

The study’s primary outcomes are as follows: (a) RISEinFAMILY implementation: proportion of families completing basic and advanced training levels (observed vs expected), average time to complete basic and advanced training levels (observed vs expected) and average time of kangaroo care per day (hours); (b) short-term health infant’s outcomes: proportion of high-risk infants achieving and maintaining adequate growth patterns during NICU admission, defined according to Patel’s method [10, 11].

The study’s secondary outcomes are as follows: reported adverse event rate per 1000 patients/day, feeding patterns and major morbidities at 36 weeks postmenstrual age (PMA) or discharge, nosocomial infection [12], necrotising enterocolitis (Bell’s > stage 2), moderate-severe brain injury (worst cranial ultrasound) [13], parental needs, empowerment and psychological health (stress [14], anxiety and depression [15, 16], self-efficacy [17], bonding [18], resilience [19]), professional’s self-care and satisfaction (anxiety and depression [15], burnout [20], post-traumatic stress [21], work and well-being [20]).

The study’s exploratory outcomes are as follows: economic impact (level of post-implementation utilisation of FICare, resources and costs associated with FICare implementation, cost-effectiveness estimates compared to the current care, expected value of current implementation and expected value of perfect implementation); mid-term infant’s general health (growth pattern during the first 12 months from birth, use of health system facilities after discharge); long-term neurodevelopment (survival without neurodevelopmental disabilities).

Specific items and test batteries are stated in Additional file 1.

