### Sample size {14}

No previous study has assessed the effect of FICare intervention on growth velocity expressed in g/kg per day. Therefore, for sample size calculation in the RISEinFAMILY project, we will follow one of the most recent studies evaluating the effect of individualised breast milk fortification on weight gain expressed in the same units [34]. In this study, based on their own data obtained in a pilot and other literature data, the authors assumed 1.8 ± 3.1 g/kg/d as a reasonable and clinically meaningful difference in weight gain. With a total *N* of 103 (experimental group *N* = 52, control group *N* = 51), they found a difference in the weight gain of 1.9 g/kg/d and a standard deviation of 2.5 g/kg/d.

Using this information, we calculated the minimum size for the intervention (FICare) and the control (standard care) group in the RISEinFAMILY study. Our null hypothesis is no impact of FICare and, as a consequence, the mean of the weight gain in both the intervention and control groups will be the same. Our alternative hypothesis is a difference in the mean weight gain between FICare and the control group of at least 1.9 g/kg/d [34]. We impose a type I error (probability of rejecting the null hypothesis when it is true) of 5% (*α* = 0.05), and a type II error (probability of not rejecting the null hypothesis when it is false) also of 5% (> 0.05), which provides a statistical power of 95%. The minimum sample size for intervention and control groups is given by at least 46 children in the intervention (FICare) and other 46 children in the control (standard care) group.

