For our primary hypothesis, we will compare infant standardised weight gain velocity between the two groups over the 4-week study period using generalised linear mixed modelling (GLMM). For our primary outcome, we will compare infant standardised weight gain between the two groups over the study period defined as the change in Patel’s growth pattern measured weekly from enrolment until day 28 post-enrolment, testing an interaction term between group and post-baseline weight measurements. We will adjust for additional covariates using a hybrid approach, forcing in known confounders of gestational age and study site and using backward stepwise selection to retain covariates that contributed *p* < 0.1 to the final model from potential confounders. Additionally, we will conduct sensitivity analyses by adding in weight measured at discharge.

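### Outcomes {12} labels six measures primary, but the sample size, the only 5% error rate and the primary model concern weight gain alone, so the protocol disagrees with itself on what is primary

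*Protocol article*

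**What the plan says.** Three sections of the protocol article bear on this.

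- **Outcomes {12}** calls two groups of measures primary in one sentence. Group (a) opens it: "The study’s primary outcomes are as follows: (a) RISEinFAMILY implementation: proportion of families completing basic and advanced training levels (observed vs expected"), then "average time to complete basic and advanced training levels (observed vs expected) and average time of kangaroo care per day (hours"). Group (b) is "proportion of high-risk infants achieving and maintaining adequate growth patterns during NICU admission, defined according to Patel’s method". Neither group is ranked above the other.
- **Sample size {14}** states one null hypothesis, that "the mean of the weight gain in both the intervention and control groups will be the same", and attaches one error rate to it: "We impose a type I error (probability of rejecting the null hypothesis when it is true) of 5" per cent. It uses a difference of 1.9 g/kg/d, a standard deviation of 2.5 g/kg/d and 95% power, and arrives at 46 infants per group. No other outcome is sized.
- **Statistical methods {20a}** writes in the singular: "For our primary hypothesis, we will compare infant standardised weight gain velocity between the two groups over the 4-week study period". The next sentence gives weight gain to day 28 after enrolment as the primary outcome. No model is set out for the group (a) measures. The same section does plan general control-versus-intervention tests (chi-square, analysis of variance, rank tests) without saying which outcomes they serve.

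**The concern.** A reader of the Outcomes section would take the trial to have six primary measures. A reader of the other two sections would take it to have one. The article does not say whether group (a), group (b), either or both must succeed.

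This matters because the two groups answer different questions. The Objectives section seeks superiority over routine care in infants' clinical outcomes, parental mental health and professionals' self-care and satisfaction. Training completion and completion time measure none of these; they describe how well the intervention was delivered. Kangaroo time is also largely a delivery measure, since a unit that trains parents and brings them into care would be expected to record more of it whether or not infants grow better. With the present labels, a null growth result alongside longer kangaroo time could be written up as a primary outcome met. The study is non-randomised and hospitals and staff are not blinded, so a success criterion fixed in advance carries extra weight.

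**Working it through.** **1. Count of measures labelled primary (Outcomes {12}).** Completion proportions, basic and advanced: 2. Completion times, basic and advanced: 2. Kangaroo hours per day: 1. Growth proportion: 1. Total 2 + 2 + 1 + 1 = 6 (4 if basic and advanced are counted together).

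**2. Where the 5% is spent (Sample size {14}).** Standardised difference d = 1.9 / 2.5 = 0.76. Normal approximation, two-sided 0.05, power 0.95:

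n = 2 × (1.960 + 1.645)² / 0.76² = 45.0 per group.

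The two-sample t-test gives 45.98, so 46, as stated. One-sided 0.05 gives 38.2, so 39, which does not match. The 46 is therefore a two-sided 5% test of one variable, mean weight gain, with nothing reserved for any other primary measure.

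**3. Which of the six can be compared with control.** The four training measures are set against an expected value. Controls receive standard care, so they have no value on these measures, and the article states no test for them. That leaves kangaroo time and growth, k = 2.

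**4. Family-wise error if both are tested at two-sided 5%.** If independent: 1 − 0.95² = 0.0975. The article gives no correlation between them, so a range is assumed:

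| Correlation | Two tests | Six tests |
|---|---|---|
| 0 | 9.75% | 26.5% |
| 0.3 | 9.5% | 24.1% |
| 0.5 | 9.1% | 20.7% |
| 0.8 | 7.8% | 13.9% |

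The other rows are the probability that at least one of k equally correlated standard normal statistics exceeds 1.96 in absolute value. The six-test column is for reference only and would require the four training measures to be tested at 5% as well.

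**5. Cost of splitting alpha instead.** At 0.05 / 2 = 0.025 for each of the two comparable measures, 95% power for growth needs 54 per group by the t-test (53 by the normal approximation), and 46 per group would give about 91% to 92%. As with the stated 46, this makes no allowance for clustering.

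**6. Which growth variable.** Side by side, the three sections use different forms:
- Outcomes {12}: a proportion with adequate growth, over the NICU stay.
- Sample size {14}: a mean, in g/kg/d.
- Statistical methods {20a}: standardised weight gain measured weekly to day 28 after enrolment.

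The growth measure on the primary list is therefore neither the variable that was sized nor the one described in the primary model.

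**The case against.** The strongest reply is that the article does rank its outcomes. It states one null hypothesis and one alpha, and uses the phrases primary hypothesis and primary outcome for weight gain only. Multiplicity rules often sit in an analysis plan, and this is a condensed article. Implementation as a primary domain also suits a project whose aim is to adapt and scale a care model.

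Much of this stands. The absence of an alpha split is not in itself a fault here, the statistical section does imply a ranking, and there is good reason to keep an implementation domain. What it does not answer is that the Outcomes section puts six measures under the primary label while two other sections treat one as primary. An analysis plan could settle that only by overriding one of them.

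It is also fair to say that a real rise in kangaroo time would be a true positive and not a type I error. Family-wise error therefore does not measure the main problem, which is what a process measure can show about benefit to infants.

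A reader might go further and infer that the trial can be declared positive on any of six measures, with a family-wise error near 21%. The article does not support that. It states no rule that any one measure suffices, and it gives no test for the four training measures. The 21% also needs six tests at 5% with an assumed correlation of about 0.5.

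**Conclusion.** The point holds as an internal contradiction: six measures are labelled primary in one section, while the sample size and the primary model treat weight gain as the only one. The stated 5% covers one test of weight gain and not the set labelled primary.

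If kangaroo time and growth are both tested between groups at two-sided 5%, the family-wise error is about 8% to 10%. That rests on an assumed correlation of 0 to 0.8 and on kangaroo time being tested as confirmatory, which the Outcomes section does not say. The six-test range of 14% to 26.5% should not be cited as the trial's error rate.

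The main consequence is interpretive: delivery measures could be presented as primary success when growth is null. The contradiction should be corrected.

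**What to change.** In Outcomes {12}, Sample size {14} and Statistical methods {20a}, name one and the same growth variable as the single confirmatory primary outcome. Continuous weight gain velocity to day 28 after enrolment is the natural choice: it is what the statistical section models and the closest to what was sized. The Patel proportion in (b) then becomes secondary. Making that proportion the sole primary outcome would leave the 46 per group and the planned model unmatched to it.

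State that the primary outcome is tested once, at two-sided 5%, by the control-versus-intervention contrast at sites 1 to 5. Keep the measures in (a) as a separate implementation domain, reported with estimates and 95% confidence intervals and no superiority claim, and say that they cannot make the trial positive when growth is null. If kangaroo time is to be confirmatory, test it at 5% only after growth is significant (fixed sequence).

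The cost is wording in the protocol, the analysis plan and the registry entry, with no extra data or infants. A fixed sequence leaves the stated 46 per group unchanged, whereas splitting alpha over two measures would raise it to about 54. The downside is that implementation results can no longer be claimed as a primary success.

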## Introduction

### Background and rationale {6a}

Family Integrated Care (FICare) promotes the active participation of family members in providing specialised care to their sick newborn baby admitted to the neonatal intensive care unit (NICU). This change in paradigm in neonatal care, initially developed and implemented at Mount Sinai Hospital in Toronto in the stable preterm infant, has shown promising results in improving health outcomes in this population. The first pilot study conducted by O’Brien et al. demonstrated that parental involvement in direct care led to better weight gain, increased breastfeeding rates, and reduced stress and anxiety levels among parents of preterm infants [1].

These findings were further supported in a cluster-randomised controlled trial [2], as well as in subsequent studies highlighting the positive effects of the model in accelerating maturation processes [3] (earlier full enteral nutrition [3, 4]) shorter duration of mechanical ventilation and hospital length of stay [5–9], decreased rates of late-onset sepsis [5, 6], and improvements in neurobehaviour at 18 months [7]. Recently, Moreno-Sanz [8] described the successful adaptation and implementation of FICare policies also in the unstable, critically ill premature infant and the high-risk neonate with complex medical or surgical conditions, suggesting the potential for generalising the FICare model as the standard of care in NICUs.

However, the FICare model has only been tested up to now in high-income, developed countries. FICare relies on structured professional and caregiver training and parental physical and psychological support, which implies the provision of resources. Yet, the scalability of the model to overcome social-cultural barriers and cost-effectiveness analysis has not been tested.

RISEinFAMILY is an international consortium that has been designed for adapting and implementing FICare in different regions of Europe and Africa. The expansion of FICare to other NICUs and countries necessitates further research to identify potential constraints that may limit its adoption, particularly in low- and middle-income countries with different sociocultural contexts. Understanding these barriers and developing strategies to address them will be crucial in realising the full potential of FICare and ensuring its successful implementation globally.

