### Eligibility criteria {10}

We will include infants born with birth weight at or below 1500 g or gestational age at or below 34 weeks, any other peri-neonatal condition anticipating NICU specialised care with an admission for at least 7 days and the decision to provide full life support. Further, we will include parents if they are willing to spend at least 6 h per day at NICU or committed to attending educational sessions, an active involvement in care of their infant for at least a 7-day period, not to have an intellectual or language barriers to understanding, at least one primary caregiver is involved in the training and signed informed consent. We will exclude infants with the decision not to provide full life support, critical illness unlikely to survive or scheduled for early transfer to another non-FICare hospital. We will exclude parents if they have an intellectual handicap that makes learning-understanding difficult, communication cannot be established even with a translator, have mental psychiatric problems or under legal supervision, or guardianship of social services, and finally, lack of parental signed informed consent.

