## Statistical methods

### Statistical methods for primary and secondary outcomes {20a}

The primary analysis will be conducted in the intention-to-treat (ITT) population including all enrolled patient-family dyads who received at least one task training according to protocol procedures.

Descriptive statistics will be recorded for each group with mean, median and standard deviation for numerical variables and absolute and relative frequencies for categorical variables. 95% confidence intervals (CIs) will be provided. Comparisons between control and intervention groups will be performed using chi-square tests for categorical variables, analysis of variance for normally distributed continuous variables, and Mann–Whitney or Kruskal–Wallis tests for non-normally distributed continuous variables. Through a mixed-methods research approach and techniques both quantitative and qualitative, the following impacts will be evaluated: (a) effect of intervention: the control and the intervention group dataset from the non-FICare-experienced centres will be compared; (b) effect of “expertise” on outcomes: comparisons will be conducted between datasets from already trained FICare centres and those from the non-FICare-experienced centres.

Socio-economic sustainability: Health economics analysis based on the value of implementation framework will be conducted to assess the cost-effectiveness of RISEinFAMILY implementation strategies. The difference between the total net benefit of perfect adoption and the total net benefit of current implementation will generate the expected value of perfect implementation (positive values would characterise cost-effective implementation strategies). The analysis will also allow identifying differences in delivering RISEinFAMILY in different countries/health care settings.

Psychological assessment of experiences collected by either the NICUs staff and the families enrolled in the pilots will be conducted. Gender differences will be explored in relation to socioeconomic and cultural background.

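### Training completion is counted only in families who committed to the training and began it, so it tends to overstate uptake and cannot by itself speak for families screened out

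*Protocol article*

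**What the plan says.** **Outcome.** Outcomes {12} in the protocol article lists as primary "RISEinFAMILY implementation: proportion of families completing basic and advanced training levels (observed vs expected"), next to time to complete training and daily kangaroo care. It states no denominator and refers to Additional file 1, which is not shown, for specific items.

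**Entry.** Eligibility criteria {10} requires parents to be "willing to spend at least 6 h per day at NICU or committed to attending educational sessions", to undertake "an active involvement in care of their infant for at least a 7-day period", and "not to have an intellectual or language barriers to understanding". It also requires a primary caregiver who takes part in the training, and signed consent. Psychiatric problems, legal supervision and social-service guardianship exclude. So does the case where "communication cannot be established even with a translator".

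**Analysis set.** Statistical methods {20a} places the primary analysis in a population labelled intention-to-treat, "including all enrolled patient-family dyads who received at least one task training".

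**Aim.** Background and rationale {6a} names the gap to be filled: "the scalability of the model to overcome social-cultural barriers and cost-effectiveness analysis has not been tested". The closing paragraph of the Discussion expects the results to support an international package whatever the differences in building, culture or economy.

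**The concern.** The outcome measures whether families finish the training. Commitment to that training, or to long daily presence, is a condition of entry, and so is having a caregiver in it. Having begun it is a condition of being analysed. Three groups therefore cannot appear as non-completers: families who fail a family criterion, families who refuse, and families who enrol but never start.

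Some of the family criteria (language, mental health, social situation, availability) overlap with the barriers that the project sets out to test. A high completion figure could be read as evidence that the model overcomes those barriers when the families who carry them were not in the count. If sites lose different shares of families before the count, equal completion figures at two sites could also go with different reach.

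Separately, the two language rules do not match. Inclusion asks for no language barrier, exclusion applies only when a translator does not help, and the Abstract speaks of no comprehension barriers. A family that communicates through a translator can be read as ineligible under the first rule and eligible under the second.

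**Working it through.** **Stated figure.** The article gives no expected completion proportion, precision or sample size for this outcome. Its one calculation, 46 per group, concerns weight gain and has no bearing here. No enrolment, start or completion rate is given either, so every rate below is an assumption.

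**Step 1: who can be a non-completer.**

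| Group | Can count as a non-completer? | Source |
|---|---|---|
| Infant eligible, family fails a family criterion | No | Eligibility {10} |
| Infant eligible, family refuses consent | No | Eligibility {10} |
| Enrolled, no task trained | No | Statistical methods {20a} |
| Enrolled, one or more tasks trained, level not completed | Yes | Outcomes {12} |

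**Step 2: effect of dropping non-starters.** Let r be completion in the analysis set and s the share of enrolled intervention-phase families who receive a first task. A family with no trained task has not completed a level, so completion over all enrolled families = r × s. With r = 80%:

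- s = 95%: 0.80 × 0.95 = 76%, overstated by 4 points
- s = 90%: 0.80 × 0.90 = 72%, overstated by 8 points
- s = 80%: 0.80 × 0.80 = 64%, overstated by 16 points

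The direction is certain whenever s is below 100%. The size is not known.

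**Step 3: effect of families not enrolled.** Let f be the share of infant-eligible families who enrol, c completion among enrolled families, and u the completion that non-enrolled families would have reached. Completion over all infant-eligible families = f × c + (1 − f) × u, and the overstatement is (1 − f) × (c − u). With c = 80% and u from 0% to 40%:

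| f | All infant-eligible families | Overstatement |
|---|---|---|
| 90% | 72% to 76% | 4 to 8 points |
| 80% | 64% to 72% | 8 to 16 points |
| 60% | 48% to 64% | 16 to 32 points |
| 40% | 32% to 56% | 24 to 48 points |

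Here the direction holds only if u is below c, which is plausible but not shown. At u = c the overstatement is zero. Steps 2 and 3 are separate illustrations, each starting from 80%, and should not be added.

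**Step 4: aim against population.** The aim and the closing claim concern scalability over social and cultural barriers. The counted population is families who passed the language, mental-health, social-situation and commitment criteria, consented and began training. The outcome informs on the first only as far as the second extends.

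**The case against.** Several counter-arguments have force.

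- **Target population.** Completion among eligible, consenting families is a proper quantity to estimate, and reach is a different one. A reader might infer that the figure is biased for its own population because families are selected. Selection on eligibility and consent does not make it so. Only the loss of enrolled non-starters distorts it, and the requirement of a caregiver in training may keep that loss small.
- **Denominator.** Outcomes {12} states none, and Additional file 1 might. Applying the primary analysis set to this primary outcome is the natural reading of Statistical methods {20a}, but it remains a reading.
- **Barriers.** A reader might infer that the trial can say nothing about social and cultural barriers. That goes too far: sites in six countries differ in culture and resources, and comparing enrolled families across them is informative.
- **Time.** A reader might take six hours a day as compulsory. The criterion offers commitment to sessions as an alternative, and the family workshops may be online or hybrid.
- **Economics.** A reader might infer that overstated completion feeds the value-of-implementation analysis. Utilisation is listed as a separate exploratory outcome, and nothing says it is derived from completion among enrolled families. It could even serve as a reach measure.
- **Replacing the outcome.** Making reach times completion the headline would score every non-enrolled family as a failure. Because the intervention changes care at unit level, some of them may still be taught.
- **Language.** The exclusion may be meant only to specify the inclusion wording.

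What remains is that non-starters are dropped under a label that implies the opposite, no primary measure covers families outside enrolment, the closing claim exceeds what enrolled families can show, and the two language phrases need aligning.

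**Conclusion.** The concern holds in a limited form. As written, completion overstates uptake among all enrolled intervention-phase families if any of them never start: by 4 to 16 points for a reported 80% if 80% to 95% start. It also overstates uptake among all infant-eligible families if those not enrolled would complete less often: by 4 to 48 points over the assumed ranges. These are illustrations, since the documents fix none of the inputs, and the first rests on the primary analysis set applying to this outcome.

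The outcome cannot by itself show that the model overcomes barriers for families screened out, so the Discussion's closing claim goes beyond it. The documents do not establish that completion will look high or similar across countries, nor that the primary outcome must be replaced. The language wording is an inconsistency to be reconciled whatever the size of the other effects.

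**What to change.** 1. Keep completion among enrolled families as the primary implementation outcome, but define its denominator as all enrolled intervention-phase families, with those who never start counted as non-completers.
2. Add a supplementary reach figure by site: families enrolled and completing, over all families whose infant meets the infant criteria. Give anonymous counts of families lost to each family criterion and to refusal, and state that non-enrolled families may still have been taught on the unit.
3. Limit the scalability conclusion to the population these figures cover.
4. Reconcile the inclusion and exclusion wording on language so that one rule applies at every site.

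**Cost.** Table 1 already makes date and eligibility at screening mandatory eCRF entries, but it does not say that non-enrolled families or reasons for refusal are logged, so a short anonymous log is needed. Enrolment began in February 2023, so counts from before the change may be incomplete and should be reported as such. The completion figure will be less favourable if some enrolled families do not start.
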